## Methods/design

The protocol has been structured according to the Standard Protocol Items: Recommendations for Interventional Trials (SPIRIT 2013 Checklist) (Appendix S1).

### Study setting

This study is a prospective, single-centre, randomized, double-blind controlled study in which 300 patients will be randomly assigned to the test group or the control group in a 1:1 allocation ratio. The study protocol can be accessed at the chictr.org.cn website (ChiCTR2100046201). Figure 1 shows the trial flow chart.

**Fig. 1 Fig1:**
[figure not shown]
Trial flow chart

### Eligibility criteria

Patients who meet any of the following conditions will be included:Patients of both sexes between 18 and 80 years old;Colon cancer (cT_3-4__a_T_0-3_M_0_ [UICC/AJCC-8th Colon Cancer TNM tumour stage]), rectal cancer (cT_3-4_N_0-3_M_0_ or any CT/N + [UICC/AJCC-8th Rectal Cancer TNM tumour stage]) and patients diagnosed and treated directly with surgery at each study centre;Patients who voluntarily agreed to join this study and signed the relevant informed consent form after verbal discussion about the clinical trial and discussion of the intention of obtaining informed consent.Patients who meet any of the following conditions will be excluded:Taking various classes of antibiotic medications on their own or with medical advice for various reasons within 2 weeks before surgery;Previous diagnosis or current diagnosis of inflammatory bowel disease;Diagnosed with acute intestinal perforation or acute small intestinal diverticulum;Those with ischaemic colitis or infectious colitis were included in the diagnosis;Diagnostic finding of other comorbid local or systemic disease that requires anti-infective treatment;Two and more simultaneous surgeries;Had been diagnosed due to acute and chronic peritonitis or other infectious diseases that require anti-infective treatment in the perioperative period;Any acute physiological disturbance that indicates that the subject requires emergency surgery without elective surgery [e.g., need for preoperative mechanical ventilation, preoperative acute renal failure, preoperative systemic inflammatory release syndrome, and sepsis or septic shock];ASA was rated on a 5-level scale;Immunodeficiency, immunosuppression or autoimmune diseases (e.g., allogeneic bone marrow transplant patients within the last 5 years, taking immunosuppressive drugs, and SLE);The subject refused to sign an informed consent form to participate in the trial;Other scenarios in which normal cooperation with a physician was not possible for personal reasons or the investigator considered it unsuitable to participate in the experiment; andAll single-port laparoscopic procedures, transhiatal procedures, and various new surgical modalities need to be used.The terminating study criteria are as follows:Subject's violation of treatment principles after enrolment (such as violation of entry criteria, noncompliance with study treatment medication or surgical arrangements);Subject was inoperable for various reasons after enrolment (reasons to be recorded);Subjects had nonstudy-related complications, such as drug hypersensitivity reactions, after enrolment;Because of the occurrence of adverse events, after the judgement of the investigator, the subject was not considered suitable to continue with the trial (the reason for withdrawal was recorded);Subjects or the subject's legally authorized representative required withdrawal from the study;Subjects developed serious complications or intolerable adverse reactions; andThe subject was not available for elective surgery after enrolment due to exacerbation of intercurrent illness or other reasons;

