### Randomization/assignment of interventions

Randomization was stratified by centre. Once informed consent is obtained, randomization will be performed via a centrally managed database. After receiving the patient grouping information, designated researchers will prepare trial drugs or placebo for patients according to the assigned group. In this process, only the researchers are informed about the grouping of patients. They will sign a confidentiality agreement and will not participate in any other links of the trial to ensure that they will not have any impact on the study. After collecting all the data, the designated researcher named the two groups A and B. The analyst will analyse the primary and secondary results without knowing the group name. Only after the analysis of the primary and secondary results can complete blindness be eliminated and ineffective blinding events recorded (for example, the study nurse discloses the patient's specific medication to the doctor).

The nurses provided the patients with oral antibiotics for the experimental group and placebo for the control group in the ward.

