### Data collection, management, and analysis

#### Clinical data

Clinical data from patients will be obtained by medical staff and recorded on an online electronic platform (Http://www.medresman.org.cn) and in the CRF table. The sample will be coded, and the patient's identity will be known only by the attending physician. The clinical data will include the following: general patient information, past medical history, past surgical history, laboratory examination results, imaging results, surgery details, postoperative infection rate, incidence of postoperative complications, incidence of anastomotic leakage, and 30-day readmission rate after surgery. The timing and processing of the above-recorded contents will all be reflected in the CRF table, and the laboratory examinations will mainly assess preoperative and postoperative routine blood and inflammatory indicators (Table 2).

**Table 2 Tab2:** CRF table

Stage	Pre-operation		Intra-operation	Post-operation						
Follow-up period	14–3 days	3–1 days		1–14 days	30 days	1–12 months	12–24 months	24–36 months	36–48 months	48–60 months
Baseline data collected	√	-	-	-	-	-	-	-	-	-
Inclusion and exclusion	√	-	-	-	-	-	-	-	-	-
Sign informed consent	√	-	-	-	-	-	-	-	-	-
Group determination	√	-	-	-	-	-	-	-	-	-
Physical examination	√	-	-	-	√	√	√	√	√	√
Imaging examination	√	-	-	-	-	√	√	√	√	√
laboratory examination	√	-	-	-	√	√	√	√	√	√
First administration	-	√	-	-	-	-	-	-	-	-
Administration	-	-	-	√	√	√	√	√	√	√
Postoperation pathology	-	-	-	√	-	-	-	-	-	-
Safety observation	-	-	√	√	√	√	√	√	√	√
Record adverse events	-	-	√	√	√	√	√	√	√	√
Other works	√	√	√	√	√	√	√	√	√	√

A detailed description of the above data is shown in the CRF table.

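### The antibiotic exclusion is timed to surgery, but eligibility is checked and patients are randomised 14 to 3 days before it, so 3 to 14 days of the window cannot be verified at entry and later events can become grounds for termination

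*Protocol article*

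**What the plan says.** Two exclusions under Eligibility criteria are timed to the operation. One covers "Taking various classes of antibiotic medications on their own or with medical advice for various reasons within 2 weeks before surgery". The other covers peritonitis or "other infectious diseases that require anti-infective treatment in the perioperative period". The termination list in the same section includes violations found after enrolment, "such as violation of entry criteria, noncompliance with study treatment medication or surgical arrangements".

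Table 2 (Clinical data) ticks "Inclusion and exclusion" and "Group determination" once each, both in the column for 14 to 3 days before surgery. "First administration" is ticked in the column for 3 to 1 days before surgery, and Table 1 (Interventions) agrees, with metronidazole or placebo on pre-operative D3–D1. The randomisation section confirms the order: "Once informed consent is obtained, randomization will be performed via a centrally managed database". It also describes the experimental treatment as an antibiotic: "The nurses provided the patients with oral antibiotics for the experimental group and placebo for the control group in the ward".

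Four other places bear on the point:
- Relevant concomitant care and interventions places no limit on concomitant care.
- Clinical data lists postoperative infection, complications and anastomotic leakage among the results collected, and complications are a secondary outcome.
- Statistical analysis specifies intention to treat for the primary endpoint and the analysis of all included subjects.
- The Introduction keeps patients discontinued for drug-related reactions in the ITT set and leaves them out of the PP set.

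**The concern.** An entry criterion should be decidable when the patient enters. Here the antibiotic window is still open at randomisation, and the infection criterion may be. Whatever happens in the open part (a course of antibiotics, an infection) happens after allocation and, from 3 days before surgery, possibly under the influence of the study drug. Because an entry violation found later is a ground for termination, the plan turns some post-randomisation events into reasons to end participation.

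If an antibiotic started before surgery changes the rate of infection, or of antibiotic prescribing for it, such terminations need not be equal in the two arms. What is at stake is completeness of the 5-year liver metastasis outcome and the make-up of any per-protocol set. There is also a practical cost: a criterion that cannot be checked at entry, and that overlaps scheduled study dosing without an exemption, will be applied differently by different staff.

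**Working it through.** The article gives no figure for this point, so there is none to reproduce. The check compares timings and then gauges the size of the consequence.

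**Step 1: how much of the antibiotic window is open at randomisation.** Inputs: a 14-day window ending at surgery (Eligibility criteria); randomisation r days before surgery, with r from 3 to 14 (Table 2). Days verifiable at entry = 14 − r. Days after randomisation = r.

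| Randomised on day | Verifiable at entry | After randomisation |
|---|---|---|
| −14 | 14 − 14 = 0 | 14 |
| −10 | 14 − 10 = 4 | 10 |
| −3 | 14 − 3 = 11 | 3 |

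Even in the best case 3 days remain open. Those are the 3 days on which Table 1 schedules study drug: 3/14 = 21% of the window.

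**Step 2: whether anything closes the gap.** Table 2 shows no second eligibility check. The antibiotic criterion has no carve-out for study drug. The termination rule refers to entry violations after enrolment without saying when the violating event must have occurred. The concomitant care section allows any treatment, which does not sit with an exclusion that a newly prescribed antibiotic could trigger.

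**Step 3: how many patients the infection criterion could touch, if read as extending past randomisation.** The article gives no infection rate. Assume 15% on placebo and 10% on metronidazole: 150 × 0.15 = 22.5 and 150 × 0.10 = 15, a gap of 7.5 patients. Across an assumed range of 5% to 20%, the count per arm runs from 150 × 0.05 = 7.5 to 150 × 0.20 = 30.

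**Step 4: the bias if all such patients were lost from the comparison.** All inputs are assumed. The drug has no effect on metastasis. Half the patients are low risk (metastasis 10%, control-arm infection 10%) and half high risk (30% and 30%). The drug halves infection.

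- Control retained: 0.5 × 0.90 + 0.5 × 0.70 = 0.80, or 120 of 150. Metastasis among them: (0.45 × 0.10 + 0.35 × 0.30)/0.80 = 18.8%.
- Experimental retained: 0.5 × 0.95 + 0.5 × 0.85 = 0.90, or 135 of 150. Metastasis among them: (0.475 × 0.10 + 0.425 × 0.30)/0.90 = 19.4%.
- Spurious difference: 0.1944 − 0.1875 = 0.0069, about 0.7 points.

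Four sets of assumptions, including this one, gave differences between 0.15 and 1.5 points. The retained numbers in the two extreme sets were 135 v 142.5 and 112.5 v 138.75. The imbalance in loss is more visible than the bias.

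**The case against.** The case for leaving this alone has four parts.

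**Study drug was never meant.** A reader might infer that every metronidazole patient breaches the antibiotic exclusion through the pre-operative doses while no placebo patient does. That is too literal. The criterion describes ordinary non-study use, eligibility is judged before the first dose, and blinded doctors and data collectors could not apply it to one arm. It should not be counted as an expected effect. What stands is that the text does not say study drug is exempt.

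**The infection criterion may refer to screening.** A reader might infer that a postoperative leak or peritonitis makes a randomised patient ineligible. The criterion speaks of a diagnosis already made, and the perioperative phrase can describe when treatment is needed. Collecting infection and leakage as results, and leaving concomitant care unrestricted, favours that reading. What stands is that the wording allows both.

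**Intention to treat protects the primary analysis.** A reader might infer that the randomised comparison is broken. The documents do not support this: all included subjects are to be analysed, and no passage removes these patients. But an intention-to-treat rule does not supply a 5-year liver outcome for someone whose participation ended early. The article does not say whether follow-up continues after termination; the full protocol may.

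**Rewording is not a complete cure.** The termination list separately covers serious complications and intolerable reactions, which are plainly post-randomisation. That is correct, and rewording the two exclusions does not close that route.

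**Conclusion.** The concern holds in a limited form. The stated timings conflict: 3 to 14 days of the antibiotic window lie after randomisation and cannot be verified at the only eligibility check. This follows from the article's own tables and needs no assumption. The infection criterion is ambiguous rather than wrong. Together with the termination rule, these criteria permit patients to be terminated for events that treatment may influence.

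The likely harm is unequal loss of follow-up and of per-protocol patients. The per-protocol part is an inference, since the only PP rule the article gives concerns drug-related reactions. The infection counts and the 0.15 to 1.5 point bias rest wholly on assumed rates, and the bias also on the premise that every affected patient is lost. Under those conditions it remains small. The point merits correction because the text cannot be applied as scheduled and correcting it is cheap, not because a large distortion of the primary result has been shown.

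**What to change.** 1. Tie the antibiotic exclusion to a period ending at or before randomisation, and state that study drug does not count as a breach.
2. Reword the infection exclusion so that it refers to a condition present at or before randomisation.
3. State that antibiotics or infections arising after randomisation are recorded as concomitant medication or outcome events, and neither make a randomised patient ineligible nor end outcome follow-up. Applying the follow-up part of that sentence to the other termination reasons as well would cover the route that the rewording leaves open.
4. Reconcile Eligibility criteria (including the termination list), Relevant concomitant care and interventions, Table 2 and Statistical analysis, so that they agree.

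Whether surgical prophylaxis needs its own exemption is for the sponsor, since the article does not describe it. So is whether study treatment continues after any such event; the statistical request concerns outcome data only.

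The cost is two reworded criteria and a few clarifying sentences. The downside is that a few patients exposed to antibiotics between randomisation and surgery stay in the trial. The article gives no figure for how many.

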The long-term effects of metronidazole use cause serious side effects and have been reported as individual cases in recent years. The probability of developing peripheral neuropathy in patients who continue to take metronidazole for > 4 weeks (taking a total dose of > 42 g) for a long period of time is approximately 17.9% [11, 12]. According to calculations, the blood concentration is approximately 34–45 μg/ml when patients develop peripheral neuropathy, and nearly all patients experience symptom resolution after discontinuing the medication. Therefore, for this study, we set the duration of metronidazole administration to 5 years in our patients, and because anaerobes are extremely sensitive to metronidazole, the dosage was extremely low, and in addition to long-term regulatory follow-up, patients in this protocol only needed to maintain daily blood concentrations greater than 0.01 μG/ml, which can maximize patient safety. At the same time, all the studies with patients who showed drug-related adverse reactions were discontinued, which was included in the ITT set and not included in the PP set.

The aim of this prospective, single-centre, large sample, randomized controlled trial is to demonstrate that long-term oral antibiotics can effectively reduce the incidence of post-operative liver metastasis in patients with colorectal cancer. Secondary objectives included safety and acceptability of the drugs used, treatment-related morbidity and mortality, and relevant follow-up.

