#### Statistical analysis

The association with the variables of interest will be compared between groups by means of Pearson’s chi-squared test or Fisher’s exact test, as appropriate and in the case of categorical variables. For continuous variables, Student’s *t* test for independent samples and the Mann–Whitney *U* test will be used for normally and nonnormally distributed variables, respectively.

The analysis for the primary end-point variable (incidence of postoperative liver metastasis) will be performed with an intention-to-treat approach. The absolute difference in terms of incidence will be computed, along with 95% confidence intervals, and will be expressed as relative risk or odds ratio, as appropriate for each outcome.

An interim analysis is planned, once 50% of the patients have completed their treatment (half of the patients per arm). The study can be suspended if the treatment superiority is statistically significant, with a *P* value set at <0.0052. The interim analysis will be performed in agreement with previously reported epidemiological and statistical criteria.

For the secondary variables, a similar approach will be used, using the effect estimate with a 95% confidence interval and the relative risk and odds ratio for categorical variables.

Any potential effects related to centres or surgeons will be assessed by means of mixed models. For the primary end-point variable, a bivariate and multivariate analysis will be performed to identify the potential effects of other variables.

The value for statistical significance at the final analysis was set at *P* < 0.05. Statistical analysis will be performed with SPSS 20. All the deviations from the original statistical plan will be described and justified. All subjects included in the study will be included in the analysis.

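### The termination criteria do not separate stopping study drug from leaving the study, so 5-year outcome collection is undefined for patients whom the intention-to-treat analysis must include

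*Protocol article*

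**What the plan says.** All of this is in the protocol article.

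- **Eligibility criteria.** One list of termination criteria, with one consequence, covers "violation of treatment principles after enrolment (such as violation of entry criteria, noncompliance with study treatment medication or surgical arrangements"; inoperability or unavailability for surgery; adverse events after which "the subject was not considered suitable to continue with the trial (the reason for withdrawal was recorded"; and "Subjects developed serious complications or intolerable adverse reactions". A request by the subject or representative to withdraw stands in the same list.
- **Introduction.** On drug-related reactions: "patients who showed drug-related adverse reactions were discontinued, which was included in the ITT set and not included in the PP set".
- **Interventions and Outcomes.** Dosing is tentatively set at 5 years, the same horizon as the primary outcome, which is the incidence of liver metastasis within 5 years after surgery.
- **Statistical analysis.** The primary analysis is by intention to treat, incidences are compared by chi-squared or Fisher's exact test, and "All subjects included in the study will be included in the analysis".
- **Written informed consent.** Patients are asked whether data may be used if they opt out. This concerns use of data, not continued assessment.

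**The concern.** Intention to treat needs the 5-year liver status of every randomised patient, whether or not the patient stays on drug. A list that treats non-compliance or an adverse reaction in the same way as withdrawal of consent invites sites to stop visits and imaging along with the tablets. Because treatment is meant to last as long as follow-up, this can happen at any point in the outcome window.

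An analysis plan can choose how to handle a missing status, but it cannot recover imaging that was never done. If the loss also differs by arm, the randomised comparison on the primary outcome is exposed to a bias whose sign and size cannot be established afterwards.

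**Working it through.** **1. The passages side by side.** The adverse-event criterion speaks of not continuing with the trial and of withdrawal, which describes leaving the study. The Introduction and Statistical analysis require the same patients in the analysis. No section says that they are followed to 5 years, and none says that outcome collection stops. The text is therefore unreconciled on the one fact that the primary analysis needs.

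**2. Inputs for the size.**
- The plan gives no termination rate to reproduce. Its nearest figure is about 17.9% peripheral neuropathy with metronidazole for more than 4 weeks and more than 42 g in total (Introduction). For 150 patients per arm: 0.179 × 150 = 26.9, about 27.
- True 5-year incidence: 20% in both arms, so no drug effect. This is an assumption, the middle of the 15 to 25% in the Introduction.
- Constant hazard: λ = −ln(0.80)/5 = 0.0446 per year.
- Termination time τ: 0.15 years (about 8 weeks) to 1 year (assumed).
- Placebo terminations: 0% or 5% (assumed).

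**3. Terminated patients counted as event-free after termination.** With a proportion q terminated, observed incidence = (1 − q) × 0.20 + q × (1 − e^(−λτ)).
- Metronidazole, q = 0.179, τ = 0.15: 0.1642 + 0.179 × 0.0067 = 0.165.
- Metronidazole, q = 0.179, τ = 1: 0.1642 + 0.179 × 0.0436 = 0.172.
- No placebo terminations: 0.165/0.20 = 0.83 and 0.172/0.20 = 0.86.
- Placebo q = 0.05: placebo incidence is 0.1903 and 0.1922, so the relative risk is 0.87 and 0.90.

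**4. Other counting rules.** Here 27/150 = 18% of the metronidazole arm is terminated before any event, with 20% true incidence.

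| Rule for terminated patients | RR, 0% placebo loss | RR, 5% placebo loss |
|---|---|---|
| Event-free | 0.82 | 0.86 |
| Dropped, loss unrelated to risk | 1.00 | 1.00 |
| Dropped, at twice the risk of the others | 0.85 | 0.89 |
| Dropped, at half the risk of the others | 1.10 | 1.07 |
| Counted as events | 1.72 | 1.43 |

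In the dropped rows, the risk among those remaining is 0.20/(qk + 1 − q), where k is the risk ratio of terminated to remaining patients. For q = 0.18 and k = 2 this is 0.20/1.18 = 0.1695, and 0.1695/0.20 = 0.85.

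**5. False findings for metronidazole.** These come from exact enumeration of two binomials of 150 with the uncorrected chi-squared test at two-sided 0.05 (the article does not state sidedness). Under the event-free rule at 20%, the chance of a significant result in favour of metronidazole is 12.5% with no placebo loss and 8.5% with 5%, against a nominal 2.5%. Across control rates of 15 to 25% the range is 7.1 to 15.1%. If terminated patients are followed completely, it returns to 2.5% and the expected relative risk is 1.00.

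**The case against.** A reader might infer that the plan loses outcomes unequally and in favour of metronidazole. The documents do not support that as stated.

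- No passage says that outcome collection stops. Keeping patients with drug reactions in the ITT set and removing them only from the PP set is also compatible with continued follow-up.
- No passage says how a terminated patient is counted. That rule may sit in a full protocol or analysis plan that is not shown, so its absence is no finding. The table shows that the direction depends on it.
- Event-free counting with no placebo loss is an extreme case. Placebo patients also have surgery, chemotherapy and a long course of study medication, and most of the criteria are not specific to metronidazole.
- Entry violations and inoperability have no evident reason to differ by arm under blinding. Only adverse reactions, and non-compliance that follows from them, plausibly do.
- The 17.9% is a figure for long-term use, and the Introduction argues that its low dosing limits this harm.

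All five points stand, and they limit the claim. On the last, if the 1 g in Table 1 is a daily dose (an assumption), 3 preoperative days plus 21 days per 28-day cycle pass 42 g in week 7: 3 + 21 = 24 g by the end of the first cycle, and 42 g after 18 more dosing days. The Auditing section also expects side effects. Unequal loss therefore remains likely, although 17.9% is only illustrative.

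The objections do not remove the core. The list as written ends participation for treatment-related reasons, and that is a stated rule, not a detail left to another document.

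**Conclusion.** The point holds in limited form. The termination criteria, on their plain reading, end participation for patients whom the Introduction and Statistical analysis require in a 5-year intention-to-treat analysis, and nothing states that their outcome is still collected. Loss is probably higher on metronidazole; the direction of bias is unknown.

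The spurious relative risks of 0.83 to 0.86, or about 0.87 to 0.90 with 5% placebo terminations, are illustrations. They rest on 20% true incidence, a constant hazard, 17.9% terminated within about 8 weeks to 1 year, and event-free counting. They are not a prediction.

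The matter deserves correction because, if sites follow the list as written, the missing primary-outcome data cannot be recovered at analysis.

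**What to change.** Reconcile the Eligibility criteria, Introduction and Statistical analysis sections as follows.

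1. Separate discontinuation of study treatment from withdrawal from follow-up. Leave the clinical reasons for stopping treatment as they are, and keep withdrawal of consent as its own category.
2. State that every randomised patient who stops treatment or is found ineligible continues the Table 2 imaging and survival follow-up to 60 months, unless consent to follow-up is withdrawn.
3. State how the primary outcome is defined for the few unresected patients, because an outcome counted from surgery gives them no starting point.

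Two wider changes are not needed. Relabelling the whole list as reasons to stop study drug would misdescribe withdrawal of consent and turn other items into drug-stopping rules. Starting the outcome clock at randomisation would change the stated endpoint.

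The cost is protocol wording and modest follow-up effort for patients off treatment, most of it already scheduled. The exception is unresected patients: Table 2 places all follow-up imaging under its postoperative columns, so any imaging for them would be an addition.

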## Introduction

The liver is the most prominent target organ for haematogenous metastasis of colorectal cancer. Fifteen to 25% of patients with colorectal cancer have combined liver metastases at the time of diagnosis, and an additional 15 to 25% will develop liver metastases after curative resection of primary colorectal cancer, with the vast majority (80–90%) of liver metastases unresponsive to curative resection at first. Colorectal cancer liver metastasis is also the leading cause of death in patients with colorectal cancer.

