### Outcomes

#### Primary outcome

Efficacy will be measured in terms of the incidence of postoperative liver metastasis within 5 years after surgery.

Assessment will be conducted by in-person visits; should the status of the pandemic impact the study with no possibility of performing in-person 5-year follow-up appointments, telemonitoring might be considered using validated tools.

Considering that the dose of metronidazole is predicted in the form of a hypothesis, the incidence of drug-related adverse events will be regarded as one of the main indicators of this study.

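### The terminating criteria end trial participation after adverse events (and, by their heading, noncompliance), yet the ITT analysis of 5-year liver metastasis needs those patients' outcomes

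*Protocol article*

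**What the plan says.** All places are in the protocol article.

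- **Eligibility criteria, terminating list.** There is one list, headed as criteria for terminating the study. Its adverse-event item applies when, in the investigator's judgement, "the subject was not considered suitable to continue with the trial (the reason for withdrawal was recorded"). Other items are "noncompliance with study treatment medication or surgical arrangements" and "Subjects developed serious complications or intolerable adverse reactions". The list also covers violation of entry criteria and drug hypersensitivity reactions. No separate rule covers stopping the study drug alone.
- **Introduction, on metronidazole safety.** The text says that "all the studies with patients who showed drug-related adverse reactions were discontinued, which was included in the ITT set", and excludes these patients from the per-protocol set.
- **Primary outcome.** Efficacy is "the incidence of postoperative liver metastasis within 5 years after surgery".
- **Statistical analysis.** "The analysis for the primary end-point variable (incidence of postoperative liver metastasis) will be performed with an intention-to-treat approach". The result is a comparison of proportions: chi-squared or Fisher test, absolute difference, relative risk or odds ratio. The section closes with "All subjects included in the study will be included in the analysis".
- **Table 2.** Imaging is scheduled in every column to 48–60 months. Drug administration is a separate row ticked in the same postoperative follow-up columns. Nothing is said about patients who have stopped the drug.
- **Patient protection/written informed consent forms.** Participants are asked whether their data may be used if they opt out. Continued outcome collection is not mentioned.

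**The concern.** A 5-year proportion analysed by intention to treat needs the 5-year liver status of every randomized patient. The adverse-event item ends the participation under which that status would be collected. Assigning a patient to the ITT set does not supply a scan that was never done, and no later analysis plan can recover it.

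The loss would probably be unequal. Both arms undergo surgery and receive chemotherapy, so patients will leave both. Reactions to metronidazole itself, however, add exits mainly in one arm. If withdrawn patients stay in the denominator and their unseen metastases count as none, metronidazole looks protective without being so. If their status is left unknown, the ITT result cannot be computed without assumptions.

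The point concerns the stated conduct rule that creates the missing outcomes. How missing outcomes would be handled belongs to an analysis plan and is not criticised here.

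**Working it through.** **The texts side by side.** The Introduction and Statistical analysis sections require that patients stopped for drug reactions be counted. Primary outcome requires their liver status over 5 years. The adverse-event item speaks of the trial and of withdrawal, and nothing elsewhere in the article restores follow-up for these patients. The noncompliance and intolerable-reaction items do not use those words; they rest on the list's heading.

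**Inputs from the document.** 150 patients per arm; final P < 0.05 (taken as two-sided); background incidence from the Introduction, where "an additional 15 to 25% will develop liver metastases after curative resection of primary colorectal cancer", with 20% as the midpoint. The only rate available as an anchor for drug-related exits is the Introduction's 17.9% for peripheral neuropathy after more than 4 weeks and more than 42 g of metronidazole: 150 × 0.179 = 26.9, about 27 patients.

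**Assumptions not in the document.** No true drug effect; a share f of withdrawn patients' metastases goes unseen (0.9 unless stated); unseen metastases are counted as none; withdrawal rates w as shown.

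**Formula.** Apparent incidence in an arm = p × (1 − w × f). The false-benefit rate is the probability that Pearson's chi-squared test gives P < 0.05 in favour of metronidazole, by exact enumeration of the two binomial distributions (150 v 150).

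Example, 17.9% v 5% at p = 0.20:
- metronidazole: 0.20 × (1 − 0.179 × 0.9) = 0.168
- placebo: 0.20 × (1 − 0.05 × 0.9) = 0.191
- apparent RR: 0.88

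| Withdrawn, metronidazole v placebo | Apparent incidence | False-benefit rate |
|---|---|---|
| none | 20.0% v 20.0% | 2.5% |
| 5% v 2% | 19.1% v 19.6% | 3.3% |
| 10% v 5% | 18.2% v 19.1% | 3.9% |
| 17.9% v 10% | 16.8% v 18.2% | 5.1% |
| 17.9% v 5% | 16.8% v 19.1% | 7.6% |
| 17.9% v 0% (extreme) | 16.8% v 20.0% | 10.8% |

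**Sensitivity of the extreme row (no placebo withdrawal).** At 15% and 25% incidence the rate is 8.7% and 12.9%. With only half of the metastases unseen it is 5.9%. At half the withdrawal rate (8.95%) it is 5.4%, and at about one tenth (1.8%) it is 3.0%. With every metastasis in withdrawn patients unseen, a normal approximation gives 12.3% at 20% incidence.

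**If the outcomes are left unknown.** With 27 of 150 unknown and 20% incidence in the other 123, 0.20 × 123 = 24.6 events are seen. Metronidazole-arm incidence then lies between 24.6/150 = 16.4% and (24.6 + 27)/150 = 34.4%. These are logical bounds; the upper one has all 27 metastasising, so the span is not an expected error.

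**The case against.** The strongest reply is that the list may mean only coming off protocol treatment. It never says that imaging or survival contact stops, and the Introduction counts these patients in the ITT set, so the sections could be read as consistent: off drug, still analysed as randomized. The article condenses a fuller protocol that may provide for follow-up off drug. In Table 2, imaging and administration are separate rows, so shared ticks do not make imaging depend on taking the drug.

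Part of this stands. Table 2 does not prove that follow-up ends, the consent sentence on opting out settles nothing either way, and for noncompliance and intolerable reactions the case depends on the heading alone. The benign reading nevertheless strains against the adverse-event item's own words, which name the trial and withdrawal. An investigator following them would take the patient out. The point rests on that stated rule and not on a missing detail.

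The objection to size also stands. A reader might take 10.8% as the expected error rate. The document does not support that: it states no rule that counts unseen outcomes as none, the 17.9% comes from other patients and may not apply at this trial's intended plasma level, not every neuropathy case need leave the trial, and placebo patients will leave too.

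A reader might also infer that removing noncompliant patients favours metronidazole in the same way. In a double-blind trial the document gives no reason to expect noncompliance to differ by arm in a particular direction.

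**Conclusion.** The concern holds as a conflict between a conduct rule and the primary analysis. Followed as worded, the adverse-event item loses 5-year outcomes for treatment-related reasons in patients whom the ITT analysis must count. The heading extends this, less firmly, to intolerable reactions and noncompliance.

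The consequence is modest to moderate. At 20% incidence with no true effect, 90% of withdrawn patients' metastases unseen and unseen counted as none, the false-benefit rate is roughly 3% to 8% against 2.5% when withdrawal is 5% v 2% up to 17.9% v 5%. The 10.8% needs 17.9% v 0%. Every withdrawal rate here is an assumption, and the expected direction applies to drug-reaction withdrawals only. The sponsor should make the change, since follow-up skipped after withdrawal may be impossible to rebuild.

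**What to change.** Separate stopping the drug from leaving the study. In the terminating criteria under Eligibility criteria, put in substance:

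*An adverse event, serious complication, intolerable or hypersensitivity reaction, noncompliance, or entry-criteria violation found after randomization stops metronidazole/placebo only. The patient stays on the Table 2 imaging and survival schedule to 60 months. Follow-up ends early only at death or if the patient withdraws consent to follow-up.*

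Align the Introduction: *Patients who stop study medication for a drug-related reaction stay in the ITT set, with follow-up to 60 months, and are excluded from the PP set.*

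Which reactions stop the drug remains the sponsor's clinical decision.

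Cost: a protocol amendment through the investigator meeting and ethics filing that the article already describes; one consent-form sentence saying that stopping the drug does not end follow-up, with possible re-consent of patients already enrolled; and the already scheduled visits and scans for patients off drug (about 27 in the metronidazole arm at the illustrative 17.9%, plus any on placebo). Endpoint, test and sample size do not change.
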